# **Purpose**

This document details the planned analyses and endpoint derivations for the 09HN study. It focuses on the analyses for the main clinical paper.

# **Statistical software**

The data derivations and statistical analyses will be performed with the statistical software R using the current R version at the time of the final analysis.

# **Analysis population and definition of baseline**

The main population for all analyses is the population of all subjects for which the primary endpoint could be defined by the endpoint review committee (modified intention-to-treat). All analyses will be according to the randomized diagnostic arm.

The following participant will be excluded from the modified intention-to-treat population:

- Patients who discharged or died before the culture flagged positive (DISCHARGE.DischargeDate + DISCHARGE.DischargeTime before SAMPLE.GDetectedDate + SAMPLE.GDetectedTime).
- Patients where the endpoint review committee felt the culture was not in itself enough to guide therapy (e.g. potential contaminant, viridans strep in a patient without signs of endocarditis),.

Baseline is defined as the time point when the participant’s first culture flagged positive.

All patients excluded from the modified intention to treat population and reasons for exclusion will be summarized by diagnostic arm (“MALDITOF MS” or “ROUTINE DIAGNOSTICS”).

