# **Primary endpoint: proportion of patients on optimal antibiotic treatment within 24 hours of positive culture (first growth of an eligible specimen)**

## **Derivation**

A patients is defined to be on optimal antibiotic treatment within 24h of positive culture (first growth of an eligible specimen) according to the endpoint committee.

As a conservative measure, patients in the modified intention-to-treat population who withdrew or died within 24 hours of positive culture will be classified as not being on optimal antibiotic treatment by 24 hours unless the optimal antibiotic treatment was already started while the subject was still in the study and alive, similarly those where the endpoint committee judged that they could not classify the outcome as the organism was not the only reason for antimicrobial therapy will be classified as not being on optimal therapy.

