## The following extra analyses were added on 13/9/17

Mortality as a binary outcome – inpatient death + patients given palliative discharge vs other

Time from culture positive to time report received on ward.

Analyse those not given appropriate therapy (ie not optimal and reason is not covered) at 24 hours and compare between arms.

Summarise reasons for non-optimal therapy in each arm

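### Mortality, discharge outcome, stay and drug use are analysed only in a committee-restricted population that they do not need, and the SAP does not say that the restriction is made independently of arm

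*SAP*

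**What the plan says.** The SAP section on analysis population and definition of baseline sets a single population: "The main population for all analyses is the population of all subjects for which the primary endpoint could be defined" (by the endpoint review committee). It is called modified intention-to-treat and is analysed by randomised arm. Two groups are removed:

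- "Patients who discharged or died before the culture flagged positive", determined from recorded dates and times;
- patients where the committee "felt the culture was not in itself enough to guide therapy", with potential contaminants and viridans streptococci without evidence of endocarditis as examples.

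The same section requires excluded patients and the reasons to be tabulated by arm (MALDI-TOF MS or routine diagnostics).

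The sections on DDDs, antibiotic duration, hospital and ICU stay, and discharge outcome name no other population. The one variation is an informal survivors-only summary for drug use and stay, which narrows the set further. The list of analyses added on 13/9/17 includes "Mortality as a binary outcome – inpatient death + patients given palliative discharge vs other", again with no population of its own.

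The derivation of the primary endpoint adds that patients for whom the committee "could not classify the outcome as the organism was not the only reason for antimicrobial therapy will be classified as not being on optimal therapy". Those patients therefore stay in.

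**The concern.** Limiting the primary endpoint to patients whose culture could guide therapy has a rationale, because optimal treatment is hard to define otherwise. That rationale does not carry over to death, discharge status, length of stay or drug consumption. These come from dates, the drug log and discharge status, whatever the committee thought of the culture.

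The second exclusion is a judgement made after randomisation. Its examples depend partly on the species found, and the arms are two ways of finding the species. If the committee works from the result that the allocated method produced, a non-guiding culture may be recognised more often in one arm than in the other. The patients left in the two arms would then differ in mix, and outcomes that randomisation would otherwise have balanced could differ with no true effect. The SAP states neither that the ruling is blind to arm nor that it rests on a common reference identification.

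**Working it through.** **Reading check.** The SAP gives no exclusion rate, mortality rate or sample size, so it has no figure to reproduce. The textual question is whether any of these outcomes needs the committee's ruling:

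- hospital stay: discharge and admission dates;
- ICU stay: admission, transfer and discharge dates;
- antibiotic duration: the drug log;
- DDDs: drug, dose, route, frequency and days given;
- ordinal discharge outcome and mortality: status at discharge.

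None does. The first exclusion is settled when the culture turns positive, before any identification result, so the organism argument does not touch it. Only the second exclusion is at issue.

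**Illustration for mortality, with no true effect. All inputs are assumed.** Let c be the share of patients with a non-guiding culture, g = 20% the mortality with a guiding culture, n = 8% the mortality with a non-guiding culture, and e the share of non-guiding cultures that is excluded in an arm. Mortality in the restricted set is then

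m(e) = [(1 − c)·g + c(1 − e)·n] / [(1 − c) + c(1 − e)].

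Take e = 100% in one arm and 50% in the other. The first arm has m = 0.200, odds 0.2500.

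- c = 10%: the second arm has (0.90×0.20 + 0.05×0.08)/0.95 = 0.184/0.95 = 0.1937, odds 0.2402. OR = 0.2500/0.2402 = 1.04.
- c = 15%: the second arm has (0.85×0.20 + 0.075×0.08)/0.925 = 0.176/0.925 = 0.1903, odds 0.2350. OR = 0.2500/0.2350 = 1.06.

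With 90% against 70% excluded and the other inputs unchanged:

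- c = 10%: 0.1808/0.91 = 0.1987 against 0.1824/0.93 = 0.1961, OR 1.02.
- c = 15%: 0.1712/0.865 = 0.1979 against 0.1736/0.895 = 0.1940, OR 1.03.

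If e is the same in both arms, or if n = g, the OR is 1.00. Bias needs both unequal exclusion and unequal prognosis.

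**Wider assumptions.** With c from 10% to 30%, n from 5% to 30% and g still 20%, the spurious OR runs from 0.96 to 1.07 at 90% against 70% excluded, and from 0.90 to 1.19 at 100% against 50%. The direction depends on which arm excludes more and on which group has the worse prognosis. The SAP settles neither.

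**Precision for mortality.** The variance of the log OR scales with 1/[N·p(1 − p)]. Compare the set without the committee exclusion (overall p) with a set that drops every non-guiding culture in both arms (p = 0.20, p(1 − p) = 0.16):

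- c = 10%: p = 0.90×0.20 + 0.10×0.08 = 0.188; SE ratio = √[0.188×0.812/(0.90×0.16)] = √(0.1527/0.1440) = 1.03.
- c = 15%: p = 0.85×0.20 + 0.15×0.08 = 0.182; SE ratio = √[0.182×0.818/(0.85×0.16)] = √(0.1489/0.1360) = 1.05.

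On these inputs the restriction widens the mortality standard error by about 3–5%.

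**The case against.** The strongest reply is that the mechanism is not in the document. The SAP does not say which identification the committee sees, when it sees it, or whether it knows the arm. Such details commonly sit in a protocol or committee charter, and neither is at hand. The viridans example also turns on a clinical finding as well as the species. A reader might infer that the committee uses the arm's own result, or that bias has been shown. The text supports neither, and with a blinded ruling on a common reference the bias would be small. This part of the reply stands, and it is why the point is conditional.

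Second, every number above is assumed, and the resulting odds ratios are mostly close to 1. That also stands. The figures show only what could happen.

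Third, the plan analyses by randomised arm and tabulates exclusions with reasons by arm, and calling this the main population does not bar another. The table is a real safeguard for detection, but it does not repair a comparison that proves unbalanced. No other set is defined for these outcomes, apart from the still narrower survivors.

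Two other inferences go too far. A reader might say that data are lost with nothing gained. In fact, leaving out patients whose culture could not guide therapy may avoid some dilution of a true effect. A reader might also take the precision loss for mortality as 1/√0.90 to 1/√0.85, or 5–8%. That treats the excluded patients as being as informative as the rest, which does not fit an assumed mortality of 8% against 20%.

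**Conclusion.** The point holds in a modest, conditional form. For mortality, discharge outcome, stay, DDDs and antibiotic duration, the SAP applies a restriction that these outcomes do not need. It rests partly on a post-randomisation judgement linked to organism identity, and the SAP does not state that this judgement is independent of arm.

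Whether this biases anything is unknown. It requires exclusion shares that differ by arm and a prognosis that differs between excluded and retained patients. On the main assumed inputs the spurious mortality OR is 1.04–1.06 and the loss of precision is 3–5%. Neither figure comes from the SAP. The document does not support the claim that randomisation has been broken.

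The edge of the population is also unclear. It is defined by endpoints that could be determined, yet the primary endpoint derivation keeps some patients whom the committee could not classify. Outcomes that need no ruling should not depend on where that line falls.

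**What to change.** For mortality, the ordinal discharge outcome, hospital and ICU stay, DDDs and antibiotic duration, make the main analysis all randomised patients still in hospital when the first culture turned positive, by randomised arm. This drops only the committee-judgement exclusion. Show the present modified intention-to-treat set as a sensitivity analysis for these outcomes. Leave the primary endpoint population unchanged, and keep the by-arm table of exclusions. It would also help to state whether the exclusion ruling is made blind to arm and on which identification.

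The cost is SAP wording and a second run of models already specified, provided that the drug log and discharge record were completed for the excluded patients. The SAP already dates its later additions, and this one can be dated in the same way. The downside is that patients whose culture could not guide therapy may slightly dilute any true effect. The sensitivity analysis would help to show how far the results depend on including them.

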# **Primary endpoint: proportion of patients on optimal antibiotic treatment within 24 hours of positive culture (first growth of an eligible specimen)**

## **Derivation**

A patients is defined to be on optimal antibiotic treatment within 24h of positive culture (first growth of an eligible specimen) according to the endpoint committee.

As a conservative measure, patients in the modified intention-to-treat population who withdrew or died within 24 hours of positive culture will be classified as not being on optimal antibiotic treatment by 24 hours unless the optimal antibiotic treatment was already started while the subject was still in the study and alive, similarly those where the endpoint committee judged that they could not classify the outcome as the organism was not the only reason for antimicrobial therapy will be classified as not being on optimal therapy.

## **Planned analysis**

The number (%) of patients receiving the optimal antibiotic treatment within 24 hours of positive culture will be described by diagnostic arm overall and in pre-defined subgroups (see below).

For the formal comparison between the two diagnostic groups, we will use a logistic regression model of the primary endpoint depending on the treatment groups, with additional adjustment for the first specimen type (blood vs. other) and the hospital. The main effect measure is an odds ratio of optimal antibiotic treatment within 24 hours between treatment groups and a corresponding two-sided 95% confidence interval (CI) and p-value. P-values ≤0.05 are considered significant.

The analysis will be implemented using the R function glm.

The reasons why subjects were not on optimal antibiotics therapy within 24 hours will be summarized descriptively as frequency of reasons (%) amongst patients without optimal treatment.

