# **Secondary endpoint**

## **Optimal therapy within 48hrs of positive culture**

This endpoint will be analysed in the same way as the primary endpoint.

Where the endpoint is Unknown and the patient was discharged <24 hours after admission, the endpoint should be changed considered not optimal unless recorded as optimal.

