## **The time from first growth of an eligible specimen to optimal antibiotic treatment**

**Derivation**

Duration between the two events = Date-time of optimal treatment – Date-time of first growth of an eligible specimen.

Patients who received optimal antibiotics treatment will have the event type “received optimal antibiotics treatment”. Patients who did not receive documented optimal antibiotics treatment will be considered as having a competing event “death without prior optimal treatment” at their death date (if they died prior to receiving optimal treatment) or a competing event “discharge/other without optimal treatment” at their hospital discharge date.

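### The primary and 48-hour logistic models leave out the baseline value of their own outcome: valid, but less precise than they could be, by an amount the SAP does not let one fix

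*SAP*

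**What the plan says.** All references are to the SAP.

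- **Time zero** (analysis population section): "Baseline is defined as the time point when the participant’s first culture flagged positive".
- **Primary outcome** (derivation under the primary endpoint), which a review committee judges: "A patients is defined to be on optimal antibiotic treatment within 24h of positive culture (first growth of an eligible specimen) according to the endpoint". No rule excludes or separates patients whose treatment was already optimal at the flag.
- **Primary model** (primary endpoint, planned analysis): logistic regression on arm, "with additional adjustment for the first specimen type (blood vs. other) and the hospital", fitted with R's glm. The result is expressed as follows: "The main effect measure is an odds ratio of optimal antibiotic treatment within 24 hours between treatment groups". It is reported with "a corresponding two-sided 95% confidence interval (CI) and p-value", and the threshold is worded "P-values ≤0.05 are considered significant".
- **48-hour endpoint**: "This endpoint will be analysed in the same way as the primary endpoint", so it has the same covariates.
- **Time from first growth to optimal treatment** (derivation): "Duration between the two events = Date-time of optimal treatment – Date-time of first growth of an eligible specimen". The companion endpoint restarts the clock at specimen collection.

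Treatment status at the flag does not appear among the baseline characteristics, the primary covariates, the subgroups or the analyses added on 13/9/17.

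**The concern.** A patient whose empirical treatment was already optimal at the flag will very probably be a success at 24 hours in either arm. Faster identification can change the result only for patients not yet on optimal treatment. Status at the flag is therefore likely to be the strongest single predictor of the outcome, yet the model adjusts for two others and not for this one.

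Two things are at stake. Precision is lost, because variation between already-optimal and not-yet-optimal patients, including any chance imbalance between arms, stays in the comparison. The odds ratio is also pulled towards 1 relative to its value among patients whose result was still open.

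The variable looks derivable from data the SAP already uses. The time-to-event endpoint needs both date-times. The version timed from specimen collection requires treatment starts between collection and flag to be dated.

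**Working it through.** The SAP gives no sample size, event rate, target effect or share already optimal, so there is no figure of its own to reproduce. From the SAP come the outcome, the covariates, the two-sided 95% interval and the 0.05 threshold. Everything else below is assumed.

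**Notation.** b = share already optimal at the flag; s = proportion of those who count as successes; p = mean success proportion over both arms.

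**Route 1: variance reduction.** Assume 60% against 70% success (p = 0.65) and 80% power without the covariate.

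- rho = b(s − p) / √[b(1 − b)p(1 − p)]
- adjusted power = Φ(2.80/√(1 − rho²) − 1.96)

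Example, b = 0.3 and s = 1: rho = 0.105/0.2186 = 0.48; 1 − rho² = 0.769; power = Φ(3.19 − 1.96) = 0.89.

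| b | s = 1: rho, power | s = 0.95: rho, power |
|---|---|---|
| 0.1 | 0.24, 82% | 0.21, 82% |
| 0.2 | 0.37, 85% | 0.31, 84% |
| 0.3 | 0.48, 89% | 0.41, 87% |
| 0.4 | 0.60, 94% | 0.51, 90% |

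A simulation of 4,000 trials per setting (354 per arm) agrees: 83%, 86%, 89% and 94% for s = 1, and 82%, 84%, 87% and 89% for s = 0.95.

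Two sensitivities matter:

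- **Lower s.** With b = 0.3 and s = 0.80, rho = 0.045/0.2186 = 0.21 and power is about 82%, a gain of about 2 points.
- **Other control rates.** At b = 0.1, control rates of 50% to 70% give gains of about 1 to 4 points. At a 70% control rate (p = 0.75) and b = 0.4, rho = 0.10/0.212 = 0.47 for s = 1 and 0.08/0.212 = 0.38 for s = 0.95. Power is then about 89% and 86%, gains of 9 and 6 points. At a 50% control rate the gains are larger than in the table.

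**Route 2: logistic simulation.** Assume 0.40 against 0.55 success among patients not yet optimal, 300 per arm, with hospital and specimen type in both models.

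| b | s | SAP model | With status at flag |
|---|---|---|---|
| 0.2 | 1 | 84% | 90% |
| 0.4 | 1 | 64–67% | 80–83% |
| 0.4 | 0.95 | 64% | 75% |

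The two values at b = 0.4, s = 1 come from two runs. In closed form, b = 0.4 makes the overall rates 0.64 (0.4 + 0.6 × 0.40) and 0.73 (0.4 + 0.6 × 0.55). These need 417 per arm for 80% power, against 289 when only the open results carry information. At b = 0 the models do not differ.

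**Validity.** In 8,000 null trials per setting (b = 0.2, 0.4, 0.6; s = 1, 0.95), the rejection rate was between 0.046 and 0.055 for both models.

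**Dilution.** In route 1 with b = 0.3 and s = 1, the odds ratio without the covariate is (0.70/0.30)/(0.60/0.40) = 1.56. Among patients not yet optimal, the rates are (0.60 − 0.30)/0.70 = 0.429 and (0.70 − 0.30)/0.70 = 0.571, an odds ratio of 1.78.

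**Fitting.** If every already-optimal patient succeeds, maximum likelihood quasi-separates. In simulation the status coefficient drifted to about 25 with a standard error in the thousands, while the arm estimate remained usable.

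**The case against.** The strongest reply is that nothing here is an error. The model names its covariates and holds its type I error. Chance imbalance in an unmodelled covariate is ordinary sampling variation, which the confidence interval already reflects. **That stands.** A reader might infer from the dilution and the imbalance that the planned primary result is biased or its p-value untrustworthy; neither the text nor the null simulations support this.

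Second, the share already optimal may be small. The analyses added on 13/9/17 separate non-optimal patients who were not covered from the rest, so a patient could be covered without being optimal. The SAP also collects reasons for not streamlining treatment. If optimal treatment usually means streamlining once the organism is known, few patients would qualify at the flag. **That also stands**: a gain of only 1 to 4 points cannot be excluded. A reader might infer that the trial is underpowered, but the SAP gives no figure from which to say so.

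Third, timing. The SAP records additions made while the manuscript was being drafted, a note that an outcome turned out skewed and was log-transformed, and further analyses dated 13/9/17. Replacing the primary model after arm-level results were known would be a post-hoc change, and a power argument cannot justify it. **This limits the remedy but does not remove it.**

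Fourth, practicalities. The SAP describes committee classification at 24 hours, not at the flag, and does not say how treatment started before the flag is dated. Availability without new data is therefore a reasonable inference, not a stated fact. Quasi-separation, unclassifiable patients and small subgroups each need a rule. All can be met by wording.

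**Conclusion.** The point holds as one of efficiency and interpretation. Both logistic models omit the baseline value of their outcome. The planned analysis remains valid but gives up precision whenever some patients are already optimal at the flag and mostly stay so.

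Under the assumptions shown, adjustment gains about 1 to 4 power points at b = 10%, about 4 to 6 at 20% and roughly 10 or more at 40%, provided at least 95% of those patients remain successes. The last figure falls to 6 to 9 points if the control rate is 70%. If only 80% remain successes, the gain at b = 30% is about 2 points.

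These sizes rest on assumed rates, because the SAP states neither b nor the planned sample size or effect. They also assume that the arm cannot influence treatment before the flag, which the choice of baseline supports but does not state. Reporting b by arm would settle how much the omission matters.

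**What to change.** 1. **Derive one yes/no variable**: optimal treatment started at or before the flag, from the date-times of the first-growth endpoint. Use one committee definition, applied blind to arm. State how patients the committee could not classify are coded, for example as no, to match their handling in the primary endpoint.
2. **Report it by arm** in the baseline table.
3. **Add a model that also adjusts for it**, for the 24-hour and 48-hour endpoints. Take the arm's p-value and interval from the likelihood ratio and profile likelihood, or use a Firth or stratified analysis, because of quasi-separation. Allow the term to be left out of sparse subgroups.
4. **Fix its status.** If arm-level results have not been seen, make it the primary model and keep the present one as a sensitivity analysis. If they have been seen, as the late edits suggest, keep the present model as primary and label the adjusted one a sensitivity analysis.
5. **Show a standardised risk difference beside the odds ratio.** The adjusted odds ratio is conditional on baseline status and larger (1.78 against 1.56 in the example), so the two are not interchangeable.

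The cost is SAP wording, one derived column and a check that treatment starts before the flag are dated. No new patients are needed and, if that check succeeds, no new data.

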## **Subgroup analyses**

The analysis of the primary outcome will also be performed in the following pre-defined subgroups:

- First specimen type: blood / other
- Hospital
- Type of pathogen in first culture: Fungal, bacterial, or other (mixed)
- Type of bacteria in first culture (amongst those with bacteria detected in the culture): Gram positive / Gram negative
- Admitted from home/transferred from another hospital
- Final diagnosis: Meningitis /other final diagnosis

Treatment effects in subgroups will be estimated in the same way as for the whole population, i.e. subgroup analyses will also be adjusted by specimen group and hospital unless the adjustment variable is part of the subgroup definition. Heterogeneity of the treatment effect across subgroups will be tested using likelihood ratio tests for an interaction between the treatment assignment and the respective sub-grouping variable.

